### Follow-up and end-points

The number and grade of acute allograft rejection episodes will be collected for a period of one year following transplant surgery. Data on all-cause mortality within the first year will be collected. Because all transplant centers are required to report their data to the transplant registry, we anticipate no loss to follow-up or missing data regarding rejection or death.

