### Sample

A sample of 325 adult heart transplant recipients will be recruited from the Columbia University-New York Presbyterian Medical Center (CU-NYP), the University of California, Los Angeles (UCLA), and Cedars Sinai Medical Center (CSMC) in Los Angeles, CA. Respectively, demographic characteristics at these sites are: male (68.9%, 75.7%, and 79.7%); White (53.1%, 59.1%, 73.4%); Black (20.3%, 9.4%,12.5%); Latino (14.5%, 19.9%, 9.4%) and Asian (11.3%, 10.5%, 3.1%) [1]. Inclusion criteria are: 1) ≥ 18 years of age, 2) first heart transplant surgery within six weeks of their transplant surgery, 3) not enrolled in other research studies that conflict with the study design, 4) clinically stable at time of enrollment (i.e. no clinical symptoms of allograft impairment with ejection fraction ≥ 45%).

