### Procedures

Participants will be recruited either while they are in the hospital for transplant surgery, or if that is inconvenient, during their first clinic visit following transplant surgery. After informed consent is obtained, demographic and clinical data will be collected by self-report and by medical record audit. At the time of each EMB, data from the medical record will be abstracted to confirm current medications, serum levels of anti-rejection medications, clinical data regarding EMB results, and other clinical data reflecting myocardial performance consistent with rejection status. Only one anti-rejection medication (tacrolimus) is associated with an increased QT interval. If a patient is on chronic tacrolimus therapy without a change in dosage, it should not interfere with the daily ECG monitoring measurement because we will be comparing each patient with him/herself and noting any change from the previous day's QT interval. However, we will track initiation or change in any QT-prolonging drug. On their website, the Arizona Center for Education and Research on Therapeutics [15] maintains a comprehensive list of QT- prolonging drugs that we have incorporated into the medications section of our electronic database system. Further, on a quarterly basis, we will continue to reference this website for new drugs as they come to market and update our data capture to include those associated with QT-prolongation.

The other drug class that patients may be taking is 3-Hydroxy-3-Methyl-Glutaryl Coenzyme A Reductase inhibitors (i.e., statins) which are known to shorten the QT interval. Thus, we will also monitor statin therapy. To insure patient safety, we will notify patients' transplant cardiologists within 48 h of the detection of any QTc interval exceeding the population 99th percentile for adult males (> 470 ms) or females (> 480 ms) [16].

At the time of informed consent and enrollment, subjects will receive the HeartView™ recorder and its companion Internet Transmitter, which will transmit the subject's ECG as described earlier. Subjects will be asked to record a 10-s 8-lead ECG daily for 6 months.

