### Statistical analysis

Using the variable definitions in Table 2, a logistic regression analysis will be performed with the independent variable being presence/absence of the ECG criteria (ΔQT_C _≥ +25 ms × 3 days [10]) and the dependent variable being presence/absence of acute allograft rejection. Odds ratios and confidence intervals will be reported as well as the universal proportions used to determine the value of new diagnostic criteria (sensitivity, specificity, positive/negative predictive value, and predictive accuracy, Table 3).

**Table 2 T2:** Variable definitions for statistical analysis

Variable	Definition	Type of Variable
ΔQT_C_	≥ +25 ms increase in QT_C _interval from previous day lasting 3 consecutive days [10]	Continuous (expected range, 10-100 ms)

Acute allograft rejection	EMB category 1R or 2R or 3R with confirmation by treating physician	Categorical; dichotomous (yes/no) No = 0; Yes = 1R or 2R or 3R

Days to rejection	Number of days from first positive ECG criterion to mild, moderate, or severe rejection diagnosis. If the ECG criterion follows rejection, a negative # of days will be reported.	Continuous (expected range -365 to +365)

Acute rejection severity	EMB category: 1R (mild), 2R (moderate), 3R (severe)	Categorical

Cardiac rhythm	Sinus rhythm, atrial fibrillation, atrial flutter, junctional rhythm	Categorical

Heart rate	Heart rate per minute calculated from 30 s rhythm strip	Continuous (expected range, 60-120)

P wave duration	Interval from beginning to end of P wave in ms (measure of intra-atrial conduction delay)	Continuous (expected range, 70-126 ms)

QRS duration	Interval from beginning to end of the QRS waveform	Continuous (expected range, 72-160 ms)

PR interval	Interval from the beginning of the P wave to the beginning of the QRS complex measured in ms. PR interval > 200 ms indicates an abnormal delay of conduction (1^st ^degree AV block).	Continuous (expected range, 112-240 ms)

QRS amplitude	Height of QRS waveform in μV	Continuous (expected range, 500-1000 μV

T_PEAK _- T_END_	Interval from the peak of the T wave (or nadir in inverted T waves) to the end of the T wave in ms. Prolonged T_PEAK _-T_END _indicates heterogeneity of repolarization and risk for arrhythmia	Continuous (expected range, 112-240 ms)

**Table 3 T3:** Definitions of Universal Proportions

Criterion	Definition
Sensitivity	Proportion of those with acute rejection who are positive for the ECG criterion

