## Discussion

An increased QT_C _interval in heart transplant recipients is linked to acute allograft rejection and death. Normal variation in QT_C _intervals over 24 h due to changing autonomic nervous system tone does not occur in heart transplant recipients because transplant surgery causes denervation of the allograft. Thus, an increase in QT_C _is likely to indicate cellular dysfunction that occurs with acute rejection. Prior research is inadequate to determine whether monitoring the QT interval would be valuable to detect acute allograft rejection because the studies have been retrospective and involved just a few ECGs recorded periodically and analyzed by investigators who were not blinded from information about rejection episodes.

The NEW HEART study focuses on the potential for future reduction in the number of EMBs which transplant recipients must endure in the first year following transplantation. While EMB remains the gold standard for detection of cellular rejection in heart transplant recipients, it is costly, inconvenient, and not without risk [4,5,26]. Increased QT_C _has been linked to acute allograft rejection, but has not been systematically evaluated in prospective studies. This investigation will provide "real world" prospective data to determine the sensitivity and specificity of QT_C _as an early non invasive marker of cellular rejection in transplant recipients during the first post-transplant year.

A non-invasive indicator of early allograft rejection in heart transplant recipients has the potential to limit the number and severity of rejection episodes by reducing the time and cost of rejection surveillance and by shortening the time to recognition of rejection. Additionally, achievement of the aims of the current study may identify other ECG parameters relevant for non-invasive allograft rejection monitoring and may provide support for a randomized controlled trial to determine the efficacy and cost-effectiveness of this type of noninvasive ECG monitoring compared with standard EMB surveillance.

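### Rejection is collected for a year from transplant, ECGs cover only six months from enrolment, and no timing rule keeps unmonitored rejections out of the accuracy figures

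*Protocol article*

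**What the plan says.** **Rejection period.** Follow-up and end-points: "The number and grade of acute allograft rejection episodes will be collected for a period of one year following transplant surgery". The Methods part of the Abstract gives the same period.

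**ECG period.** Procedures: "At the time of informed consent and enrollment, subjects will receive the HeartView™ recorder and its companion Internet Transmitter", and "Subjects will be asked to record a 10-s 8-lead ECG daily for 6 months". Sample allows enrolment "within six weeks of their transplant surgery". Monitoring is therefore counted from enrolment and rejection from transplant.

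**State at entry.** Sample asks for clinical stability, explained as "no clinical symptoms of allograft impairment with ejection fraction ≥ 45" per cent or more. It does not exclude a patient who has already had a biopsy graded as rejection.

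**Analysis variables.** Table 2 defines acute rejection as a per-patient yes/no: any grade from 1R to 3R, confirmed by the treating physician, with no dates. In Table 3, sensitivity is the share of rejecting patients who are positive on the ECG criterion, and specificity is the corresponding share among those without rejection. Neither definition mentions when the two events occur. Predictive accuracy is divided by all enrolled patients, so nobody is set aside as unmonitored. The days-to-rejection variable is listed as "Continuous (expected range -365 to +365".

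**Claimed scope.** The Discussion says the study will give the sensitivity and specificity of QTc as an "early non invasive marker of cellular rejection in transplant recipients during the first post-transplant year". The Abstract makes the same claim.

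**The concern.** Sensitivity describes how a test performs in people to whom it was applied. Here the test stops after six months of recording, while the event it is judged against is collected for a year from transplant. A patient whose only rejection is on day 300 could not have been detected, yet is counted with the rejecting patients. If the criterion was never met, that is a miss. If it was met months earlier for an unrelated reason, that is a hit.

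The same happens at the start. Biopsies are weekly or biweekly in the first two to three months (Diagnosis of acute allograft rejection), and grade 1R counts as rejection. A patient enrolled in week 6 may therefore already have had a qualifying biopsy before the first ECG.

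Sensitivity and negative predictive value are affected most directly. Positive predictive value and specificity can also move, because a late rejection turns an earlier false alarm into a true positive and takes that patient out of the non-rejecting group. The stated purpose is to reduce biopsies, so the negative predictive value carries much of the practical weight.

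**Working it through.** The article gives 325 patients without a target precision or power, so there is no planned figure to reproduce. The check has three parts.

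**1. Coverage.** Inputs: rejection period day 0 to 365 (Follow-up and end-points); enrolment from day 0 to day 42 (Sample); six months of ECGs, taken as 182.5 days (Procedures).

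| Enrolled on day | ECGs end on day | Days without ECG before | Days without ECG after | Uncovered share |
|---|---|---|---|---|
| 0 | 182.5 | 0 | 182.5 | 182.5/365 = 50% |
| 42 | 42 + 182.5 = 224.5 | 42 | 365 − 224.5 = 140.5 | (42 + 140.5)/365 = 50% |

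The uncovered time is half the year whatever the enrolment day. The criterion cannot be met after about day 225, so days to rejection cannot fall below about −225. The lower limit of −365 in Table 2 is unreachable.

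**2. Effect on sensitivity.** Let f be the share of rejecting patients with no rejection inside their ECG period, and c the probability that such a patient is nevertheless positive. Then

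observed sensitivity = 0.77 × (1 − f) + c × f.

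The 77% is the sensitivity reported in Table 1 for a rise of more than 25 ms. The article does not give f, so it is assumed. For c, 0.04 is 1 − 0.96, from the specificity of the same cited study. The value 0.20 is an assumed higher rate for repeated daily testing.

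| f | c = 0.04 | c = 0.20 |
|---|---|---|
| 0 | 77.0% | 77.0% |
| 10% | 0.693 + 0.004 = 69.7% | 0.693 + 0.020 = 71.3% |
| 20% | 0.616 + 0.008 = 62.4% | 0.616 + 0.040 = 65.6% |
| 30% | 0.539 + 0.012 = 55.1% | 0.539 + 0.060 = 59.9% |

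For scale, the 26% one-year rejection rate in Background gives 0.26 × 325 = 84.5 rejecting patients. The 95% half-width at 77% is 1.96 × √(0.77 × 0.23/84.5) = 9.0 points. At f = 20% the shift is 14.6 points (c = 0.04) or 11.4 points (c = 0.20), more than the sampling error. A larger sample would not remove it.

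**3. Effect on the other measures.** Take f = 20% and c = 0.04, with a 4% alarm rate in all patients who have no monitored rejection. Then 16.9 rejecting patients lie outside monitoring and 67.6 inside.

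- *As written:* true positives 52.1 + 0.7 = 52.7; false negatives 15.5 + 16.2 = 31.8; true negatives 0.96 × 240.5 = 230.9; false positives 9.6. Negative predictive value 230.9/262.7 = 87.9%; positive predictive value 52.7/62.3 = 84.6%.
- *Monitored rejections only, the other 16.9 counted as having none while monitored:* true positives 52.1; false negatives 15.5; true negatives 0.96 × 257.4 = 247.1; false positives 10.3. Negative predictive value 247.1/262.7 = 94.1%; positive predictive value 52.1/62.3 = 83.5%.

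Specificity stays at 96% here only because the same alarm rate was assumed in both groups. It moves if late rejecters alarm more or less often than patients who never reject.

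**The case against.** The strongest reply is that collecting data for a year is not the same as analysing it for a year. The one-year period suits the mortality aim, primary aim 1 speaks of the first six months, and the section on diagnosing rejection quotes a six-month rate. A six-month intent is plausible, and the article never says outright that twelve-month rejections enter the accuracy table. That uncertainty stands and lowers confidence. But aim 1 limits the QT increase to six months, not the rejection, and the Abstract and Discussion state the accuracy claim for the first year. A six-month limit from transplant would also leave the gap before enrolment.

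A second reply is that evaluable windows belong in a full protocol or analysis plan that is not shown. That would hold if the article were silent. Instead it sets out the variable definitions and accuracy formulas, and these misclassify patients if followed.

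Some stronger readings are tempting but not supported:

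- A reader might take the ±365-day range as proof that no window is applied to sensitivity. It belongs to the aim 2 timing variable and is only an expected range. It is consistent with an unwindowed analysis but does not establish one.
- A reader might infer that half of all rejections are lost because half of the time is uncovered. Biopsies become less frequent after two to three months, so the late share may be small. The article's rates (25 to 35% at six months, 26% at one year) cannot yield f, since the one-year figure is not above the six-month range.
- A reader might call the up to 42 days before enrolment the days of highest risk. The article says only that biopsies are frequent then. Six weeks is also the latest entry; recruitment is planned in hospital or at the first clinic visit.

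**Conclusion.** The point holds as a mismatch of periods combined with definitions that do not correct for it. That half of the rejection period has no ECG follows from the text. That unmonitored rejections are scored as misses or chance hits follows from Tables 2 and 3 taken literally.

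The size is not known. The sensitivities of 70%, 62% and 55%, or 71%, 66% and 60%, are illustrations resting on an assumed f and an assumed c. Their 77% starting point comes from a retrospective study with two ECGs per subject, not from this study's daily three-day criterion. The unreachable −365 limit is a minor correction and changes no estimate.

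This should be fixed before analysis, with medium confidence, because the twelve-month reading of the primary analysis is inferred rather than stated.

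**What to change.** 1. For aims 1 and 2, restrict acute allograft rejection in Table 2 to biopsies taken between the first evaluable ECG run and the last ECG. State how patients whose only rejection lies outside that period are classified.
2. In Table 3, count the criterion as a true positive only if it is met before that biopsy and within a pre-specified interval, for example since the previous biopsy. The article has no such interval, so one must be chosen. Without it, an unrelated alarm long before a monitored rejection still counts as a hit.
3. Report rejections before enrolment and after monitoring ends separately, the later ones as a prognostic analysis.
4. Correct the lower limit of days to rejection to about −225.
5. Limit the accuracy claims in the Abstract and Discussion to the monitored period.

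The change uses data already planned. It costs the work of settling the interval and some precision. Starting from 84.5 rejecting patients and 77% sensitivity, restricting the denominator at f = 20% leaves 67.6, and the 95% half-width becomes 1.96 × √(0.77 × 0.23/67.6) = 10.0 points instead of 9.0.

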### Data management

To insure accuracy of data collection, all sites will use a secure web-based data capture site, Research Electronic Data Capture (REDCap) [25], which is sponsored by a consortium of 118 research institutions. REDCap offers a stream-lined process for rapidly building a database, an interface for data collection and validation, and automated export procedures for download to statistical packages. As part of our pilot study, we developed, initiated, and refined a REDCap database which is ready for use in the proposed study.

### Statistical analysis

Using the variable definitions in Table 2, a logistic regression analysis will be performed with the independent variable being presence/absence of the ECG criteria (ΔQT_C _≥ +25 ms × 3 days [10]) and the dependent variable being presence/absence of acute allograft rejection. Odds ratios and confidence intervals will be reported as well as the universal proportions used to determine the value of new diagnostic criteria (sensitivity, specificity, positive/negative predictive value, and predictive accuracy, Table 3).

**Table 2 T2:** Variable definitions for statistical analysis

Variable	Definition	Type of Variable
ΔQT_C_	≥ +25 ms increase in QT_C _interval from previous day lasting 3 consecutive days [10]	Continuous (expected range, 10-100 ms)

Acute allograft rejection	EMB category 1R or 2R or 3R with confirmation by treating physician	Categorical; dichotomous (yes/no) No = 0; Yes = 1R or 2R or 3R

Days to rejection	Number of days from first positive ECG criterion to mild, moderate, or severe rejection diagnosis. If the ECG criterion follows rejection, a negative # of days will be reported.	Continuous (expected range -365 to +365)

Acute rejection severity	EMB category: 1R (mild), 2R (moderate), 3R (severe)	Categorical

Cardiac rhythm	Sinus rhythm, atrial fibrillation, atrial flutter, junctional rhythm	Categorical

Heart rate	Heart rate per minute calculated from 30 s rhythm strip	Continuous (expected range, 60-120)

P wave duration	Interval from beginning to end of P wave in ms (measure of intra-atrial conduction delay)	Continuous (expected range, 70-126 ms)

QRS duration	Interval from beginning to end of the QRS waveform	Continuous (expected range, 72-160 ms)

PR interval	Interval from the beginning of the P wave to the beginning of the QRS complex measured in ms. PR interval > 200 ms indicates an abnormal delay of conduction (1^st ^degree AV block).	Continuous (expected range, 112-240 ms)

QRS amplitude	Height of QRS waveform in μV	Continuous (expected range, 500-1000 μV

T_PEAK _- T_END_	Interval from the peak of the T wave (or nadir in inverted T waves) to the end of the T wave in ms. Prolonged T_PEAK _-T_END _indicates heterogeneity of repolarization and risk for arrhythmia	Continuous (expected range, 112-240 ms)

**Table 3 T3:** Definitions of Universal Proportions

Criterion	Definition
Sensitivity	Proportion of those with acute rejection who are positive for the ECG criterion

Specificity	Proportion of those without rejection who are negative for the ECG criterion

Positive Predictive Value	Proportion of patients with positive ECG criterion who have rejection

Negative Predictive Value	Proportion of patients with negative ECG criterion who do not have rejection

Predictive Accuracy	$\frac{\#\text{true positives}\pm \text{true negatives by the ECG criterion}}{\text{Total }\#\text{ of patients enrolled in the study }\times \text{ 1}00}$

Descriptive statistics (means ± SD) will be used to describe the average time period between the development of the ECG criterion and biopsy evidence of rejection. In addition, we will report the proportion of subjects who develop the ECG criterion (≥ +25 ms increase in QT interval from previous day lasting 3 consecutive days [10]) before, during, or after the stages of mild, moderate, and severe rejection.

The Kaplan-Meier method with the log-rank test will be used to estimate survival curves over one year and to compare all-cause mortality in patients who are positive or negative for the QT_C _criterion. Cox Proportional Hazard modeling will be used to control for baseline differences between groups and for tacrolimus use.

Logistic regression will be used with the dependent variables of rejection (yes/no) and all- cause mortality (yes/no). In both regressions, tacrolimus dosage (with "0" entered if the patient is not receiving tacrolimus) will be included as a covariate in the model. If any of the explorative variables are statistically significant, a multiple logistic regression model will be used including the ECG criterion of interest to determine whether additional ECG criteria are independent predictors of rejection and death.

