### Analysis of ECG monitoring data

The ECG will be sent to a large server hosted by the UCSF Office of Academic and Administrative Information Systems (OAAIS). The server is a secure, highly redundant data center with 24/7 availability due to back-up generators that protect against power outages. The system provides nightly data backup. Investigators in the [name] Lab will access the ECG data by logging on with a username and password via a Virtual Private Network (VPN), which encapsulates data transfers between networked devices not on the same private network and keeps the transferred data private from other devices. Investigators who analyze the daily ECG data will be blinded from all information regarding the subject's clinical status and biopsy results. In addition, pathologists who grade the biopsies and clinicians who provide medical care in the transplant clinics will be blinded from the QT interval monitoring data.

QT and RR intervals will be made in a computer-assisted manner. The Aerotel measurement software provides a zooming feature to enlarge ECG waveforms for better visualization. In addition, electronic calipers are provided so that the researcher will select the appropriate waveform onset and offset points and the computer software will provide the interval value in milliseconds (ms). The QT interval will be measured from the onset of the QRS waveform to the end of the T waveThe end of the T wave will be defined as the intersection of a tangent to the steepest slope of the last limb of the T wave and the baseline (Figure 2) [18]. A standardized correction to account for the effect of HR will be applied (QT_C_). An increase in the QT_C _interval from the previous day of at least 25 ms that persists for 3 consecutive days will be considered abnormal [10].

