### Diagnosis of acute allograft rejection

Rates of acute allograft rejection have varied, but the most recent rates of rejection in the first 6 months after transplant are reported to be 25 to 35% [2]. The diagnosis of acute allograft rejection is made by an EMB which will be performed in the hospital cardiac catheterization laboratory at each site. Generally, 3-6 biopsy specimens of the right ventricular endocardium are taken to minimize false negative tests. Each site will follow its own acute rejection surveillance protocol. In general, these protocols require weekly or biweekly EMBs during the first two to three post-transplant months. After that time, biopsies are performed less frequently, based on clinical judgment and risk of rejection. At each site, EMBs will be graded by clinical pathologists experienced with the heart transplant population and using the International Society of Heart and Lung Transplantation standards for acute rejection. Although early reports indicated inter-operator variability in the interpretation of EMB results [22], the use of the standardized grading system has improved the reliability and validity of the measurement. Current variability in interpretation of biopsy results occurs mainly in the diagnosis of Grade 2 rejection by local pathologists which may be misinterpreted in the presence of endocardial infiltrates called Quilty lesions [23,24]. To control for potential variability, we will monitor and record clinical and hemodynamic indicators of myocardial performance, which are obtained at the time of each biopsy or at regular clinical assessments, to support the biopsy interpretation, particularly regarding Grade 2 rejection. Such a multi-factorial approach to identification of rejection has been recommended [24].

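### The primary accuracy table counts each patient once as ECG-positive or not and once as rejected or not, with no time link, so positives after or months away from a rejection count as correct

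*Protocol article*

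**What the plan says.** All references are to the protocol article.

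- **Model (Statistical analysis).** "a logistic regression analysis will be performed with the independent variable being presence/absence of the ECG criteria"; the outcome is presence or absence of acute allograft rejection. Neither variable carries a time window.
- **Table 3.** Sensitivity is the "Proportion of those with acute rejection who are positive for the ECG criterion" and specificity the "Proportion of those without rejection who are negative for the ECG criterion". The two predictive values are proportions of patients, and predictive accuracy is divided by the number of patients enrolled.
- **Table 2, Days to rejection.** "If the ECG criterion follows rejection, a negative # of days will be reported", with an expected range of -365 to +365 days.
- **Index test.** "Subjects will be asked to record a 10-s 8-lead ECG daily for 6 months" (Procedures). A rise "from the previous day of at least 25 ms that persists for 3 consecutive days will be considered abnormal" (Analysis of ECG monitoring data).
- **Reference test.** EMBs are weekly or biweekly for the first two to three months. "After that time, biopsies are performed less frequently, based on clinical judgment and risk of rejection" (Diagnosis of acute allograft rejection). Rejection episodes are collected for one year (Follow-up and end-points).
- **Timing report (Statistical analysis).** For aim 2, the mean time between criterion and biopsy evidence is described, with the proportion of subjects positive before, during or after each stage of rejection.

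**The concern.** Aim 1 asks whether a QT increase is a sensitive and specific biomarker of rejection, and the Background gives early detection as the purpose. That is a question about an ECG change and the biopsy it precedes. The table as defined asks something else: whether patients who were positive at some time are also patients who rejected at some time.

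Three consequences follow.

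1. A patient whose first positive comes after the diagnosis is a true positive, although Table 2 foresees exactly this order.
2. A positive in the first weeks is credited with a rejection many months later. Conversely, an ECG-negative patient whose only rejection falls after monitoring ends (roughly months 7 to 12) is a false negative, although no ECG was being recorded.
3. Each further day of monitoring gives a non-rejecting patient another chance of a false alarm, and a rejecting patient another chance of a coincidental hit.

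At stake are the headline sensitivity, specificity, predictive values and odds ratio.

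**Working it through.** The article gives no false-positive rate for its rule, so no stated figure can be reproduced. What follows shows direction and range.

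**Inputs from the article.** "A sample of 325 adult heart transplant recipients will be recruited" (Sample). Rejection in the first 6 months is 25 to 35% (Diagnosis of acute allograft rejection); the midpoint of 30% gives about 98 rejecting and 227 non-rejecting patients. The 25 ms threshold had 77% sensitivity and 96% specificity in a retrospective study of 200 subjects with 2 ECGs each (Table 1).

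**Assumptions.** 180 recordings per patient, hence about 178 runs of three consecutive days; a false-positive probability p per run; independence unless stated otherwise.

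**1. Order.** If a chance positive falls uniformly over 180 days, the share falling after a rejection on day d is (180 - d)/180: 83% for day 30, 67% for day 60, 50% for day 90. All count as true positives. Only 14/180 = 7.8% fall in the 14 days before the rejection.

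**2. A marker with no signal.** Its unlinked sensitivity is 1 - (1 - p)^178, and its specificity is (1 - p)^178. With a 14-day look-back (an assumed length), its chance sensitivity is 1 - (1 - p)^14.

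| p per 3-day run | Unlinked sensitivity | Patient-level specificity | Sensitivity, 14-day look-back |
|---|---|---|---|
| 0.05% | 8.5% | 91.5% | 0.7% |
| 0.1% | 16.3% | 83.7% | 1.4% |
| 0.5% | 59.0% | 41.0% | 6.8% |
| 1% | 83.3% | 16.7% | 13.1% |

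At p = 0.01% specificity is 98.2%. Keeping 96% per patient needs p of at most 1 - 0.96^(1/178) = 0.023%.

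**3. A marker with some signal.** Apparent sensitivity is 1 - (1 - s)(1 - p)^178. With true in-window sensitivity s = 30%, it is 1 - 0.70 × 0.837 = 41% at p = 0.1%, and 1 - 0.70 × 0.410 = 71% at p = 0.5%.

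**4. How far the 3-day rule protects.** I used simulated 180-day series with Gaussian noise and no rejection signal.
- *Reading A: all three days at least 25 ms above the day before onset.* With uncorrelated noise, specificity is about 100% at an SD of 5 ms, 94% at 7.5, 55% at 10 and 2% at 15. With day-to-day correlation of 0.8 it is about 100% at 10 ms, 96% at 12.5, 78% at 15 and 18% at 20.
- *Reading B: a fresh step of at least 25 ms on each of three days.* It is about 99% or higher throughout.

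The SDs are assumed, not taken from the article.

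**5. Illustration by biopsy window.** Suppose 77%/96% held in each of k independent biopsy windows. The Background's schedule suggests k of about 8 (biweekly for three months, about 6, plus 2) to 16 (weekly for three months, about 13, plus 3).
- Specificity = 0.96^k: 72% for k = 8, 61% for 12, 52% for 16.
- Apparent sensitivity = 1 - 0.23 × 0.96^(k-1): 83%, 85%, 88%.
- PPV at 30% rejection: 56%, 49%, 44%, against 0.77 × 0.30/(0.77 × 0.30 + 0.04 × 0.70) = 89% for a single look.
- False positives among 227 non-rejecting patients: about 63 for k = 8 and 109 for k = 16, against 9 for a single look.

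**The case against.** **Timing is not ignored.** Aim 2 is about timing, and the before/during/after proportions would let a reader see how many positives came late. That stands, and a reader should not infer that the plan overlooks timing. But those proportions never enter sensitivity, specificity, the predictive values or the odds ratio.

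**The size of the specificity loss is unknown.** A reader might infer that specificity collapses over about 180 daily tests. The article does not support that. It gives no daily or per-window false-positive rate; the 3-day rule is there to suppress isolated alarms; and the simulated range runs from almost no loss to almost total loss. The 77%/96% comes from one comparison per subject with no 3-day rule reported. Applying it to 8 to 16 windows is a scenario, and correlated false alarms within a patient would soften the fall. Enrolment may come up to six weeks after surgery, so some early biopsies precede monitoring and 16 is a high count.

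**Some of the reading is inference.** The word ever does not appear, and nothing says outright that episodes are collapsed or that time without a biopsy counts as rejection-free. Still, one yes/no on each axis, with patients as the denominator, supports no other reading.

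**An analysis plan may supply windows and clustering.** An article may leave such details out. Here, though, it states the definitions, and a plan that linked positives to biopsies would have to replace those in Table 3.

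**The stakes should not be overstated.** The article hopes to reduce the number of biopsies and perhaps support a randomized trial. It does not claim that the marker would replace biopsy.

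**Conclusion.** The structural defect holds and needs correction before the data are analysed. As defined, the primary accuracy measures do not estimate how well a QT increase signals a rejection that follows it. This rests on the definitions in Tables 2 and 3 and on the mismatch between 6 months of ECGs and one year of rejection follow-up, not on any assumed error rate.

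The direction of bias is clear: unlinked positives raise sensitivity, and longer monitoring lowers specificity and generally PPV. The size is not determined. Patient-level specificity of 72% to 52% applies only if 77%/96% holds in each of 8 to 16 independent windows. If the 3-day rule makes false alarms rare enough (0.01% per run, for example), specificity stays near 98%. A collapse of specificity is one end of that range, not a finding.

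**What to change.** Rewrite the primary accuracy analysis and Tables 2 and 3 as follows.

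- **Unit:** the biopsy or biopsy interval, with that biopsy's grade as the reference.
- **Index test:** positive only if the criterion was met in a pre-specified look-back before that biopsy, for example since the prior biopsy. Add a sensitivity analysis on window length; a 14-day cap is one option, not a figure from the article.
- **Order and period:** a positive first occurring after a diagnosis is not credited to that episode, and rejections are restricted to the ECG-monitored period.
- **Estimation:** GEE logistic regression or a patient-cluster bootstrap for sensitivity, specificity, predictive values and the odds ratio.
- **False alarms:** report the rate per patient-month over all monitored time, so that alarms outside every window remain visible.
- **Per-patient table:** keep it as descriptive.

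**Cost.** No new data are needed, since ECGs are daily and results are abstracted at each EMB. The window must be fixed before unblinding. Positives outside it are not credited, so a short window turns a genuinely early signal into a miss, while a long one admits more chance positives. Later biopsies are selected by clinical judgment and risk, so per-biopsy accuracy carries that selection and should be described with it.
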